# Comparing exercise interventions to increase persistence with physical exercise and sporting activity among people with hypertension or high normal blood pressure: study protocol for a randomised controlled trial

**DOI:** 10.1186/1745-6215-15-336

**Published:** 2014-08-28

**Keywords:** Sports, Exercise referral, Hypertension, Web-based self-help tool, Health behaviour change

## Abstract

**Background:**

Increasing physical activity is known to have health benefits for people with hypertension and related conditions. Current general practitioner referrals for gym-based exercise increase physical activity but meta-analyses show that while these are effective the absolute health risk reduction is small due to patients failing to maintain activity levels over time. This study assesses the effectiveness of two sports-oriented interventions that are intended to bridge the intention-behaviour gap and thus increase the likelihood of sustained increases in physical activity.

**Methods/design:**

Four-arm randomised controlled trial. The study tests two types of intervention that are intended to increase physical activity among currently inactive 18- to 74-year-old people with hypertension or high-normal blood pressure. This study will assess the effectiveness of a 12-week sports-oriented exercise programme, the efficacy of a web-delivered self-help tool to promote and support sports participation and healthy behaviour change and the effect of these interventions in combination. The control arm will be a standard care general practitioner referral for gym-based exercise. Participants will be allocated using block randomisation. The first author and primary analyst is blinded to participant allocation. The primary outcome measures will be time spent in physical activity assessed in metabolic equivalent minutes per week using the International Physical Activity Questionnaire 1 year after commencement of the intervention. Secondary outcomes include increased involvement in sporting activity and biomedical health outcomes including change in body mass index, and waist and hip measurement and reductions in blood pressure.

**Discussion:**

If proven to be superior to general practitioner referrals for gym-based exercise, these sports-oriented interventions would constitute low-cost alternatives. The next stage would be a full economic evaluation of the interventions.

**Trial Registration:**

Current Controlled Trials ISRCTN71952900 (7 June 2013).

## Background

The health benefits of sport and physical activity (PA) have been studied extensively. The results demonstrate that participation in PA, which includes sporting activity, is associated with a reduced risk of over 20 health conditions, including cardiovascular disease and some cancers
[1, 2]. Targeting those with the greatest levels of inactivity will subsequently have an effect on all-cause mortality
[3] and produce the highest decrease in the incidence of chronic disease. In the most recent Cochrane review of interventions intended to increase physical activity
[4], the authors conclude that: "Nevertheless interventions which provide people with professional guidance about starting an exercise programme and then provide ongoing support may be more effective in encouraging the uptake of physical activity. There is no evidence that such interventions will reduce physical activity or cause other harm. There is only very limited evidence of the long-term effectiveness of interventions” (page 12).

Individuals report numerous barriers that impede their ability to be physically active
[5]. Lack of time and access to facilities are among the most common barriers that have been identified. “Exercise on prescription” interventions that involve a health professional’s written advice to a patient to be more physically active have been used with variable success
[6, 7]. A meta-analysis of the efficacy of gym-based exercise referrals for inactive people with medical conditions
[8] suggested that while these were effective the absolute health risk reduction was small due to patients failing to maintain activity levels over time. The authors show that, across the studies, 17 sedentary people would have to be referred for one person to become moderately active. They cite a range of barriers such as a lack of self-efficacy, poor body image, poor time management, lack of social support, intimidating environments, inadequate supervision and inconvenient opening hours as limiting the efficacy of these interventions.

Given the lack of time and potential access limitations, it is important to find ways, other than face-to-face programmes, to provide individuals with information, skills, and knowledge to facilitate behaviour change. This study looks at the efficacy of two interventions intended to overcome some of the barriers identified above, both with a focus on making activity fun by linking it with entry-level sporting activity. The first is a web-based behaviour change support tool that allows users to easily find out about outlets for organised activity, form and store plans to carry out the activities and to form a log of what they have achieved. The tool provides educational material and easy access to existing health maintenance sites. The second is a 12-week sports-oriented exercise programme intended as a direct substitute for existing gym-based general practitioner (GP) exercise referral. As with the latter this will be supervised by a qualified exercise professional but participants are given a choice of entry-level sports to pursue. Sports offered will include squash, badminton (‘Badmintone’), netball (‘Netfit’), tennis, swimming, walking football, bowls, athletics (‘AthleFIT’), ‘Cardio Tennis’ and a new ‘Healthy Cycle Ride’. These activities are appropriate for participants with controlled hypertension and, in line with the Surrey Exercise and Weight Management Referral Scheme Protocol, the exercise referral professional will take into consideration any other medical conditions of participants to ensure the sessions are designed and delivered in a safe and effective manner.

Using ideas from social cognition models, both interventions introduce elements of personal choice into activity planning. Perceptions of control are known to facilitate maintained behavioural change and people are known to be more likely to continue to maintain healthy lifestyles if they have freely chosen activities than if they have been instructed to carry them out
[9]. This is a feature incorporated in both interventions. The current gym-based referral lacks this element of choice, and by introducing the fun element of sports and games the intention is that participants will become more engaged in their activity. By giving people a choice of sports/games they can choose whether to get involved in games involving others, thus adding a social element to the activity, or they can choose sport activities that can be performed on a more individual basis (for example, cycling, swimming) if preferred.

Similarly, social cognition models highlight the importance of the formation of implementation intentions and these are a central feature of the web-based intervention. Research in this field
[10] shows that good intentions to change behaviour patterns often fail as a result of people failing to make the necessary intermediate plans to achieve their goals. For example, someone may intend to go running after work but fail to do so as they have left their running shoes at home.

### The interventions

#### Interactive web tool

The internet can serve as a useful tool in providing health information to large numbers of individuals
[11] and there is evidence that among working-age adults the internet is increasingly becoming a preferred method of obtaining health information
[12]. There is a plethora of data supporting the use of web-based interventions for behavioural change
[13, 14] and to increase PA
[15–18]. Davies and colleagues’ recent meta-analysis
[16] of internet-delivered PA interventions stated that the inclusion of educational components significantly increased intervention effectiveness. Results of this meta-analysis support the delivery of internet-delivered interventions in producing positive changes in PA, especially in those who are initially inactive, though the number of studies of the initially inactive remains small. None of the studies reported explicitly targeted inactive patients with hypertension and those that targeted overweight patients tended to have relatively small samples (all less than 221).

The tool is intended to mimic a section of a GP practice website that promotes health and wellbeing. Access during the study is encouraged on a regular basis. There is evidence that changing one health risk behaviour can facilitate improvement in a second health behaviour (‘success breeds success’). Additionally, increased confidence (self-efficacy) in changing one behaviour has been shown to be associated with increased confidence in changing a second behaviour
[19]. The web intervention directs patients in the website arms to interact with a web-delivered PA intervention which is based on the principles of *Let’s Get Moving*, a public health pathway designed to increase levels of PA through individual behaviour change. There is also the opportunity to browse the host health and wellbeing website and secondarily self-refer to other web-delivered health behaviour interventions (smoking, alcohol and diet). The rationale for this type of interaction is that by allowing self-selection and sequencing of interventions over time, we will achieve positive reinforcement of the PA intervention through capture of the benefit of change in other areas of health risk behaviour, whilst avoiding the danger of ‘overloading’ patients with too much information and too many competing priorities as in a conventional, simultaneous multiple health behaviour intervention.

Increased PA will also be encouraged by means of the general information and support provided throughout the site (including a focus on incorporating PA into daily routines).

Self-selection and self-sequencing of behaviour change goals and pathways will help align the intervention with the patient’s motivations, supports principles of behaviour change such as autonomy, choice and ‘interactivity’ at a primary level, and is consistent with the evidence base on effectiveness of this type of intervention
[16].

The tool is interactive and allows patients to make plans and form implementation intentions (the detail when, where, with whom, and so forth; decisions required to enact a more general plan) and draw on information on sports availability and other health-related self-care sites. It draws on some existing UK-based web resources (for example, *Let’s Get Moving*, SPOGO online sports and physical activities database, Live Well, Active Surrey) and the main emphasis is on integrating resources into an attractive interactive site that links health care professionals to signposting of sporting opportunities.

The patient is given control over the means and frequency of prompts and reminders (either via email or text message, and so forth) and be able to create, store and review action plans. The tool uses database information to personalise reminders and identify local activity opportunities. For example ‘John’ might declare an intention to cycle more and the ‘reminder’ function will alert John to any upcoming organised cycle rides in his locality. Patients will have the facility to download plans and activity logs that they can show their GP or share with friends if they wish. To better understand people’s behaviour when using the web tool we will monitor click through rates and other indices of engagement with the tool.

#### Sports exercise referral

The evidence of the effectiveness of interventions aimed at promoting sporting activity is of mixed quality. A recent Cochrane review reported that no controlled trials existed to assess the impact of sports interventions on sports participation
[20]; however, Cavill and colleagues in a review of studies with less restrictive design criteria (for example, controlled before and after studies) are able to point to a number of studies that show positive effects of structured sports training sessions on physical and sporting activity levels
[1]. They report nine studies in which sporting interventions have led to greater participation primarily through making activity enjoyable.

Underpinning theorising about the motivations to be active are notions of utility and hedonic calculus relating back to the 18th century ideas of Jeremy Bentham
[9, 21]. The basic assumption is that if exercise is pleasurable people will be more likely to repeat the experience and conversely if past experiences of exercise are unpleasant then the motivation to repeat the experience will be diminished. Although exercise is often promoted as having positive effects on mood it is far from clear that all people experience this positive outcome, particularly when pressed to exercise on gym equipment as is the case in GP exercise referrals. Indeed in the last decade or so a number of studies have shown that many people experience negative affective states, especially if they exercise at intensities approaching their ventilatory threshold
[22–25]. It has also been shown that even at intensities below the ventilatory threshold there is considerable variability in the degree of positive affect experienced during exercise which, in turn, has been implicated as a reason why activity levels remain low for many people.

The challenge is to associate exercise with other affective responses such as those resulting from success or socialising – hence an interest in linking activity to sport rather than repetitive activity on gym equipment. Several studies
[26, 27] have shown that affective responses within an exercise session are predictive of subsequent exercise behaviour at 6 and 12 months in sedentary adults, suggesting that the nature of the experience of exercise is important in determining future exercise maintenance. Similarly it has been shown that allowing people to exercise at self-determined intensities increases affective responses during exercise and the likelihood of long-term maintenance of exercise activity
[9]. This work shows that perceptions of choice and autonomy appear to be important factors in maintaining behaviour change.

In the proposed sports exercise programme, patients will be given access to a timetable of supervised sports activities that will be available to them at a variety of dates and times in the week; for example, sessions will be available during peak and off-peak hours as well as weekends and weekdays. Patients will be able to book sessions in advance and also turn up to sessions without booking. A variety of sports activities will be included as shown in the list provided previously. Each session will be 30 minutes to 1 hour long and supervised/delivered by a qualified instructor, and will follow national guidelines for exercise referral
[28]. The sports sessions will be based around an informal and relaxed version of the sport which has been developed over the last few years by the relevant National Governing Body. For example, the tennis sessions will be based around the popular Cardio Tennis sessions which encourage participants to perform well-known tennis based actions (for example, forehand shots) at a reasonable intensity to music without the use of balls. This type of session will gently introduce patients to the aspects of the sports in a fun and friendly way without enforcing the rules and restrictions of the traditional games. Instructors will be trained in how to deliver the sports as well as important health considerations for the patients of this trial. Those sports included in the trial are offered at the sports facilities during normal timetable hours which will allow patients to continue participating after their 12-week programme.

#### Research questions and hypotheses

The primary purpose of the trial is to test the independent and synergistic efficacy of the 12-week sports-oriented exercise referral intervention and the self-help web-based intervention intended to promote sustained and increased levels of physical activity over a period of 12 months. Do these interventions separately and in combination improve these indicators and do they improve them above that expected by existing gym-based GP referral alone? The secondary questions are whether these interventions improve other clinical indicators of cardiovascular health (for example, body mass index, waist and hip measures, blood pressure and other measures that contribute to the QRisk2 risk indicator) above that expected by existing gym-based GP referral? Do these interventions increase participation in sporting activity over a period of 12 months?

The interventions individually will be regarded as successful if they lead to an average increase in activity of 100 metabolic equivalent of task (MET)-minutes per week. This equates to engaging in an extra moderate intensity activity, say brisk walking (3.3 MET) for 30 minutes per week. The new interventions will be regarded as superior to the standard gym-based referral if they increase activity levels above those of the standard care gym-based exercise by 20 MET-minutes per week.

We will assess changes in indicators relating to cardiovascular health including blood pressure, weight, and waist and hip circumference. In terms of blood pressure, the interventions will be regarded as successful if they lead to an average decrease in blood pressure of 2.5 mmHg. We will assess the proportion of the sample reducing their blood pressure by more than 10 mmHg and an intervention will be regarded as a success if more than 20% of the members of that study arm achieve a reduction greater than this. The interventions will also be deemed to have been successful in promoting sports participation if they increase sports-related activity by 100 MET-minutes per week.

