### Measures

PA will be assessed via an online questionnaire using the short-form version of the International Physical Activity Questionnaire
[29], which is a well validated measure of physical activity in a number of domains and permits the calculation of MET per minute values for activities in each domain, including leisure and sporting activity
[30]. As recent research has shown that the International Physical Activity Questionnaire can overestimate activity in sedentary individuals we will use a second validated self-report measure, the Self-Report Walking and Exercise Tables
[31] that also permits the estimation of MET minutes. We will include additional items to tap the types of sporting activity people do.

Participants will complete the GPPAQ screening tool at the beginning and end of the study for inclusion on their patient records.

Health indicators will include measures of height and weight (body mass index (BMI)), waist and hip circumference, and blood pressure. These measures will be assessed by the exercise professional at the beginning, middle and end of the 12-week exercise programme. They will be collected again at the end of the 12-month period on visiting their GP surgery. Patients will be asked to consent to the collection of their most recent blood sugar, cholesterol/high-density lipoprotein ratio and indications of whether they are receiving treatment for high blood pressure. We will ask for access to medical records to assess whether they have chronic kidney disease, diabetes, rheumatoid arthritis or atrial fibrillation. These indicators are required for the QRisk2 calculations. To assess safety we will also monitor well-being during the period of the exercise programmes. Blood pressure measurements will be taken by the research team and/or by specially trained exercise professionals using Omron M6W blood pressure monitors (Omron Health Care Co. Ltd, [name]).

General health will be assessed with the RAND SF36
[32] along with short measures of drinking (the AUDIT
[33]) and smoking behaviour (The Fagerstrom Test
[34]). These will be assessed at baseline and at 12 month follow-up.

Intervention exposure will be assessed by attendance at the exercise programme sessions. Web-tool usage will be assessed by number and duration of logins over the study period.

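### Success is defined by within-arm change with no comparator, so an intervention that adds nothing to gym referral can be called successful

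*Protocol article*

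**What the plan says.** Four success rules stand in the article under 'Research questions and hypotheses':

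- Activity, on a weekly basis: "The interventions individually will be regarded as successful if they lead to an average increase in activity of 100 metabolic equivalent of task (MET)-minutes".
- Mean blood pressure: "the interventions will be regarded as successful if they lead to an average decrease in blood pressure of 2.5 mmHg".
- Blood pressure responders: "an intervention will be regarded as a success if more than 20% of the members of that study arm achieve a reduction" of more than 10 mmHg.
- Sport: the interventions are "successful in promoting sports participation if they increase sports-related activity by 100 MET-minutes per week".

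None names a comparator, and the responder rule refers expressly to the members of one arm. The same section defines superiority separately, as activity 20 MET-minutes per week above gym referral. It gives no such criterion for blood pressure or sport. Yet it asks whether the clinical indicators, blood pressure among them, improve beyond what gym referral would achieve.

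'Intervention effectiveness' plans t-tests and baseline-adjusted ANCOVA against the control arm, similar analyses for secondary outcomes, and between-arm chi-square tests for the 10 mmHg proportion. It does not mention the success rules.

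**The concern.** The comparator is an active programme. The Abstract says gym referral increases physical activity, and the Background calls it effective with a small absolute benefit. There is no untreated arm. Change from baseline within an arm therefore contains whatever the gym or sport programme does, anything non-specific that happens over a year, and any effect of the component under test. Only the randomised contrast separates these.

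The stake is the label. An arm that does not differ from gym referral, or does worse, could be reported as having met a pre-specified definition of success, including one on the primary outcome. For blood pressure and sport there is no controlled criterion beside it to correct the impression.

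**Working it through.** **1. The plan's own figure.** The article explains 100 MET-minutes as 30 minutes of brisk walking at 3.3 MET: 3.3 × 30 = 99. This reproduces. It describes a quantity of activity and does not say relative to what.

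**2. Within-arm label against randomised effect.** Let *g* be the mean change under gym referral and *δ* the effect of the tested component, so the intervention arm changes by *g* + *δ*. Success on activity requires *g* + *δ* ≥ 100; superiority requires *δ* ≥ 20.

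- Inert web tool in the gym-plus-web arm (*δ* = 0): successful whenever *g* ≥ 100.
- Sport worse than gym (*δ* < 0): successful whenever *g* ≥ 100 + |*δ*|.
- The reverse also occurs: at *δ* = 20 the arm is superior but not successful if *g* < 80.

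The article does not give *g*, so this shows what the rule permits, not how often it would happen.

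**3. The 20% responder rule with no mean change.** Inputs:

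- Systolic SD, from 'Sample size and power calculations and randomisation': 3.8/0.27 = 14.07 mmHg. Diastolic SD: 2.1/0.17 = 12.35 mmHg.
- 500 per arm, from the same section.
- Baseline-to-12-month correlation ρ: not in the article; assumed 0.5 to 0.8.
- Normal change and equal SD at both times: assumed.

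Formulae: SD of change = SD × √(2(1 − ρ)); expected share *p* = Φ(−10 / SD of change); P(arm passes) = P(Binomial(500, *p*) > 100).

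| ρ | Systolic: SD of change | Share falling >10 mmHg | Arm passes | Diastolic: share | Arm passes |
|---|---|---|---|---|---|
| 0.5 | 14.07 | 23.9% | 98% | 20.9% | 67% |
| 0.6 | 12.59 | 21.3% | 75% | 18.3% | 14.5% |
| 0.7 | 10.90 | 17.9% | 11% | 14.8% | 0.1% |
| 0.8 | 8.90 | 13.1% | 0% | 10.0% | 0% |

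Break-even: *p* = 20% when SD of change = 10/0.8416 = 11.88, so ρ = 1 − (11.88/14.07)²/2 = 0.64 for systolic and 0.54 for diastolic pressure. Above break-even a small common fall suffices: at ρ = 0.7 a systolic mean fall of 0.8 mmHg brings the expected share to 20%; at ρ = 0.8 it takes 2.5 mmHg.

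**4. The mean rules.** The standard error of mean systolic change is SD of change/√500: 0.63, 0.56 and 0.49 mmHg at ρ = 0.5, 0.6 and 0.7. With no true change, 2.5 mmHg is about four or more standard errors away, so noise does not pass this rule. A common fall of 2.5 mmHg passes it half the time, and one of 3 mmHg 79% to 85% of the time.

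For activity the article gives no SD. At ρ = 0.5 the standard error is SD/√500. With no true change, the 100 MET-minute rule is passed 0.3% of the time at an assumed SD of 800, 7% at 1,500 and 19% at 2,500. Here too the expected result under no change fails the rule, and a shift in the mean is the route to passing. The 20% rule differs in kind: below break-even its expected result under no change is a pass, and a larger arm only makes that more certain.

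**The case against.** The strongest reply is that the randomised comparison is intact. The research questions are framed partly against gym referral, a superiority margin is stated, between-arm ANCOVA and chi-square tests are planned, and the Abstract's Discussion ties the interventions' value to proven superiority over gym referral. 'Lead to' can be read causally. A 20% benchmark of relevance can also sit beside a chi-square test without contradicting it. All of this stands. A reader might infer that the trial discards its control arm; the article does not support that. The defect is confined to the success labels.

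Other stronger readings also fail:

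- *Regression to the mean by selection.* Blood pressure eligibility rests on diagnosis and clinical records, and activity eligibility on the GPPAQ. Change is measured from a new trial baseline and, for activity, on a different questionnaire. Much of any regression may precede baseline, and the article supports no figure for it.
- *Questionnaire bias.* The article says its instrument "can overestimate activity in sedentary individuals". That would tend to inflate baseline most and bias change downward, away from 100 MET-minutes. A second self-report measure is added for this reason.
- *A different device at 12 months.* 'Measures' says of the health indicators "They will be collected again at the end of the 12-month period on visiting their GP surgery", then says blood pressure is taken by the research team and/or trained exercise professionals on a named monitor. It does not say that the assessor or device changes.
- *All the rules pass by chance.* Only the 20% rule does so readily, and only at lower correlations.

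Not fixing systolic or diastolic pressure might be settled in an analysis plan that is not shown, so it counts here only as part of restating the rule.

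**Conclusion.** The point holds for the definitions of success and not for the analysis as a whole. All four rules lack a comparator, and blood pressure and sport have no controlled success criterion. That an inert add-on to gym referral could be labelled successful follows from the wording and the article's own account of gym referral, without any assumed correlation or SD; whether it would happen depends on a gym effect the article does not quantify.

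The responder rule has the further weakness that ordinary variability can satisfy it. Its size depends heavily on the unknown correlation: from near-certain passing at 0.5 to almost none at 0.8 for systolic pressure, with a lower break-even for diastolic. It also rests on SDs back-calculated from a meta-analysis of other interventions and on normality. The mean-change rules require a shift in the mean, which may be non-specific or due to the gym programme.

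**What to change.** Define every success criterion on the randomised difference from gym referral:

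- For total activity, sport activity and mean blood pressure, use the baseline-adjusted ANCOVA already planned, with a 95% confidence interval.
- For the 10 mmHg outcome, use the between-arm difference in proportions, preferably adjusted for baseline pressure, in place of the 20% cut-off.
- State whether systolic or diastolic pressure is meant.
- Report within-arm changes descriptively only.
- Reconcile the two statements in 'Measures' on who takes the 12-month blood pressure, where and with which device.

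This is a change of wording in the hypotheses and any analysis plan and needs no new data. The cost is that success becomes harder to claim. As an indication, if 2.5 mmHg were kept as a between-arm difference, the unadjusted standard error for systolic pressure with 500 per arm is 14.07 × √(2/500) = 0.89 mmHg. Power at two-sided 5% is then Φ(2.5/0.89 − 1.96), about 80% (about 89% with the diastolic SD). An arm equal to control would reach significance in its favour about 2.5% of the time, against the pass rates tabulated above for the 20% rule.
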